### Who will take informed consent {26a}

Potential participants who have attended ED for self-harm and have received a psychosocial assessment from a mental health practitioner will be introduced to the trial and screened for eligibility by the mental health practitioner. Eligible participants will be given summary information and a copy of the participant information sheet and asked for their permission for researcher contact. An additional suitability check will be carried out by a senior clinician who will review the potential participant’s health records and use their clinical expertise to assess any potential extraneous factors which may make trial participation unsuitable for the patient. The review will focus on the presence of patterns of behaviour that may impact on the ability of someone to participate in the trial, for example, patients with a history of violence towards clinical staff, a history of psychosis, who are already in therapy or have a diagnosis of autism. It will also check whether the potential participant has been referred to or offered psychological treatment, which is likely to start within the next 6 months.

Potential participants who provide consent to contact will be contacted by a researcher to explain the study in more detail and conduct a more detailed eligibility assessment. If the potential participant meets the eligibility criteria, the researcher will invite the potential participant to provide informed, written consent. The right of the participant to refuse consent without giving a reason will be respected. Electronic methods for documenting consent may be used.

Prior to consenting participants, their right to withdraw will be explained. They will be able to withdraw from different aspects of the study such as intervention, completion of questionnaires, receipt of text messages and/or access to medical records. They can withdraw for any reason at any time without their care being affected. Identifiable data already collected with consent will be retained and used in the final study analysis.

Following consent, participants will be registered onto the trial by the local researcher via a web-based system. Participants will then be able to complete baseline questionnaires (available in Additional file no. 1). Participants will then be randomised to standard care plus intervention or standard care alone.

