### Outcomes {12}

The primary outcome measure is the difference between the two randomised groups in mean CORE-OM score at 12 months [28]. The CORE-OM is a 34-item measure, widely used in primary and secondary care services in the NHS to assess levels of psychological global distress across four dimensions of well-being, symptoms (depression, anxiety, physical and trauma), functioning and risk [28]. Quality of life (QoL) is the most important patient-centred outcome as it can capture positive life changes—although reduction in the episodes of self-harm would be expected, one does not necessarily mediate the other. Secondary outcome measures include the Social Connectedness Scale (SCS) [29], the Beck Hopelessness Scale [30] and the PHQ-9 [31]. The SCS has been included as we argue that a valued goal is interpersonal in nature; therefore, achieving this through means other than self-harm will lead to more positive social connections which we know is associated with quality of life [32]. The PHQ-9 provides a reliable and valid measure of depression severity, and the Beck Hopelessness Scale as hopelessness has been shown to be a risk factor in suicidal behaviour [33].Secondary outcomes measures assessed at 6 and 12 months post randomisation (unless otherwise indicated) include difference in mean score on the CORE-OM at 6-months;Difference in the proportion of participants with reliable and clinically significant improvement on the CORE-OM (defined as a change of five or more in the clinical score and a change in score from the clinical to non-clinical range);Difference in mean score on the Beck Hopelessness Scale (BHS) [30], a 20-item self-report inventory used to measure feelings about the future, loss of motivation, and expectations;Difference in mean score on the Patient Health Questionnaire- 9 (PHQ-9) [31], a 9-item self-report measure of depression severity used to assess mental and emotional conditions;Difference in mean score on the Social Connectedness Scale—revised (SCS-R) [29], a 20-item scale used to measure social connectedness as a sense of belonging;Difference in rates of self-reported self-harm repetition measured monthly using questionnaires and also using monthly SMS messages for the 6-month follow-up period;Difference in the time to repetition of self-harm leading to hospital attendance using routinely collected data from Hospital Episode Statistics (A&E, emergency care, admissions, and outpatient datasets).

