## Statistical methods

### Statistical methods for primary and secondary outcomes {20a}

A detailed statistical analysis plan will be finalised and agreed by the research team prior to analysis.

A single final analysis is planned after the trial is closed to recruitment and follow-up and when the full database has been cleaned and locked. Analyses will be completed by the CTRU statisticians using SAS version 9.4.

The primary analysis of CORE-OM will use mixed multilevel linear regression with repeated measures (6- and 12-month outcome) adjusted for randomisation stratification factors and baseline value, with therapist treated as a random intercept. Estimated mean treatment differences at each time point will be reported with 95% confidence interval, *p*-values and ICCs. A two-sided 5% significance level will be used for statistical endpoint comparisons, unless otherwise specified.

Secondary outcomes, reliable and clinically significant improvement on the CORE-OM, hopelessness, depression and social connectedness will be analysed using the same approach, i.e. mixed multilevel linear or logistic regression, depending on the type of outcome variable.

Secondary outcomes repetition of self-harm leading to hospital and self-reported repetition of self-harm will be analysed separately.

Cox proportional hazards, accounting for randomisation stratification factors and random therapist effect (multilevel survival frailty model) [40], will be used to test for differences in the time to first repetition and the proportion of participants attending hospital for self-harm at 6 and 12 months. Hazard ratios and corresponding 95% CIs will be presented. If a participant is lost to follow-up, they will be treated as censored. Kaplan–Meier curves will be constructed for each group.

Recurrent event analysis incorporating the timing and cumulative number of hospital attendances for self-harm will be used to test for differences in the rate of recurrent events. Estimated treatment differences will be reported as the hazard ratio with 95% confidence interval and *p*-values.

Self-reported self-harm will be summarised at each follow-up time point (monthly to 12 months).

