### Methods in analysis to handle protocol non-adherence and missing data {20c}

All analyses and data summaries will be conducted on the intention-to-treat (ITT) population which is defined as all participants randomised regardless of non-compliance with the protocol or withdrawal from the study.

If appropriate, a CACE analysis using the instrumental variable approach will be conducted to estimate the treatment effect for the primary outcome when accounting for non-compliance with the intervention.

Missing data is expected; the reasons (e.g. due to loss to follow-up, illness or at random) and mechanisms for missing data will be explored, and the proportion of missing data will be compared between the intervention and control groups and by participant baseline characteristics. The sample size calculation allowed for 25% loss to follow-up for the primary outcome.

For primary and secondary outcomes, a multiple imputation model will be built under the missing at random assumption with imputation at the individual participant level. Sensitivity analyses of the primary endpoint will be conducted to assess the impact of missing data, the choice of imputation model and the missing at random assumption, as appropriate.

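### One Cox hazard ratio is asked to compare hospital-attended self-harm at both 6 and 12 months, and the censoring rule for this records-based outcome does not say which loss to follow-up it means

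*Protocol article*

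**What the plan says.** Under Outcomes {12}, the protocol article lists as a secondary outcome: "Difference in the time to repetition of self-harm leading to hospital attendance using routinely collected data from Hospital Episode Statistics". The source is routine records, not the participant's questionnaires.

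Under Statistical methods {20a}, a Cox model adjusted for the stratification factors, with a random therapist effect, is to "test for differences in the time to first repetition and the proportion of participants attending hospital for self-harm at 6 and 12 months". On output, the article says "Hazard ratios and corresponding 95% CIs will be presented" and "Kaplan–Meier curves will be constructed for each group". No risk difference, risk ratio or odds ratio at 6 or 12 months is named. The recurrent-event analysis that follows is also reported as a hazard ratio.

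The censoring rule is one sentence: "If a participant is lost to follow-up, they will be treated as censored". The term is not defined for this outcome. Its quantified use elsewhere concerns the questionnaire outcome, in {20c}: "The sample size calculation allowed for 25% loss to follow-up for the primary outcome". The consent section {26a} lets participants "withdraw from different aspects of the study such as intervention, completion of questionnaires, receipt of text messages and/or access to medical records", so stopping questionnaires and closing access to records are separate acts.

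**The concern.** There are two points, both in {20a}.

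**Fixed-time proportions.** The plan names two time points but one model and one type of effect measure. A hazard ratio fitted over 12 months averages the whole period. The Intervention description {11a} has sessions delivered within 6 months, with one or two optional telephone contacts around months 6 and 7. The effect could therefore differ before and after month 6, which is where the plan wants a separate comparison. One averaged ratio could hide a 6-month difference, or suggest one that is absent.

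**Censoring.** A participant who stops answering questionnaires can still be seen in the hospital records. If an analyst took the censoring sentence to mean questionnaire drop-out, recorded attendances after that date would be discarded. This is the trial's records-based measure of self-harm; the alternative is self-report.

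**Working it through.** The article gives no event count, event rate, hazard ratio or power for this outcome, so there is no figure to reproduce. What follows is illustration.

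**Inputs**
- Two-sided 5% level ({20a}).
- 282 per arm (about 565/2, Sample size {14}) or 174 per arm (348/2, the revised minimum in Trial status).
- 25% loss ({14} and {20c}, stated for the primary outcome).
- Assumed: 50% of controls re-attend by 12 months. The Background says more than 50% re-attend after at least a third attendance, without a time horizon; 25–60% is used as a range.
- Assumed: constant control hazard h = −ln(0.5)/12. Therapist clustering is ignored.

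**Step 1. If hazards are proportional.** S1(t) = S0(t)^HR. With S0(12) = 0.5, S0(6) = 0.707 and HR 0.70:
- 6 months: 0.707^0.70 = 0.785, a difference of 7.7 points.
- 12 months: 0.5^0.70 = 0.616, a difference of 11.6 points (6.8–12.7 across control risks of 25–60%).

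Here HR = 1 is the same as equal proportions at every time, so the Cox test does address both.

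**Step 2. If they are not.** Share of simulated trials rejecting:

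| Scenario | Per arm | 6-month difference | Single 12-month Cox | Cox truncated at 6 months | Direct test, 6 months | Direct test, 12 months |
|---|---|---|---|---|---|---|
| A. HR 0.75 throughout | 282 | −6.5 points | HR 0.745; 62% | 42% | 41% | 60% |
| B. HR 0.6 to month 6, then 1.4 | 282 | −10.7 points | HR 0.93; 10% | 83% | 83% | 5% |
| C. No effect to month 6, then HR 0.5 | 282 | about 0 | HR 0.79; 49% | 4% | 4% | 63% |
| D. HR 0.5 in months 2–6, then catch-up to equal 12-month risk | 174 | about −9 points | HR 0.95; 5–6% | 40–43% | 44–48% | 4–5% |

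Ranges in row D are across repeated simulation runs.

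Hand check of the direct 6-month test, with power ≈ Φ((|Δ| − 1.96·SE0)/SE1), where SE0 is the pooled and SE1 the unpooled standard error:
- B: control risk 1 − 0.707 = 0.293; intervention risk 1 − exp(−0.6·6h) = 0.188; Δ = 0.105, SE0 = 0.0360, SE1 = 0.0357; power 0.83.
- D: control 0.293; intervention 1 − exp(−(2 + 0.5·4)h) = 0.206; Δ = 0.087, SE0 = 0.0464, SE1 = 0.0462; power 0.46.

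In B and D the single ratio mostly misses a real 6-month difference. In C it often rejects although nothing differs at 6 months.

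**Step 3. Events discarded if questionnaire loss censors.** Assume 25% drop out, with a 12-month risk of 60% (others 47%) or 65% (others 45%). Then λ = −ln(1 − risk)/12, and the share lost = 0.25·(risk − 1 + E[exp(−λC)]) / overall risk, with C the drop-out time. Overall risk is 0.25·0.60 + 0.75·0.47 = 0.5025, or 0.25·0.65 + 0.75·0.45 = 0.50.
- C uniform over months 0–6: E = 0.802 or 0.778; lost 20.0% or 21.4%.
- C uniform over months 0–12: E = 0.655 or 0.619; lost 12.7% or 13.5%.
- C uniform over months 6–12: E = 0.507 or 0.460; lost 5.3% or 5.5%.

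**Step 4. Effect on the hazard ratio.** Simulation with 3,000 per arm and loss at a uniform time over 12 months; full records against censoring at loss:
- Non-informative loss: 0.750 v 0.747, with 11% of events lost.
- Informative loss, same in both arms: 0.794 v 0.785, with 13% lost.
- Informative loss, base rates 35% v 15% by arm: 0.803 v 0.844, with 13% lost.

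**The case against.** **On the proportions.** A reader might infer that a Cox model cannot test the 6- and 12-month proportions at all. That is too strong. Under proportional hazards it does (step 1, row A). The wording about 6 and 12 months could also mean a fit to each horizon, and truncated fits come close to the direct test: 83% v 83% in B, 40–43% v 44–48% in D. Much of the contrast in B and D comes from setting a 6-month test against a 12-month one, and the equal 12-month risk is assumed. The Kaplan–Meier curves will also display both proportions. All of this stands. What remains is that the text specifies no truncated fits and names no fixed-time effect measure.

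**On the censoring.** A reader might infer that the plan orders record-based events to be cut at questionnaire non-response. No sentence says so. The 25% is tied to the primary outcome. Withdrawal by component ({26a}), continued data collection by default ({11b}) and the intention-to-treat population ({20c}) all fit a reading in which the phrase means losing access to records, where censoring is correct. An analysis plan that is not shown may define it. This stands too, and it reduces the point to an ambiguous rule in the stated text.

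**On deaths.** It is tempting to add that death from self-harm should count as an event. The outcome is defined by hospital attendance, so that would change the endpoint, and the censoring sentence does not mention death.

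**Conclusion.** The point holds as a correction worth making to one secondary outcome. A single 12-month hazard ratio does not supply the two fixed-time comparisons that the plan announces, and it can mislead when hazards are not proportional. The size (about 5–10% rejection against 44–83%) rests on an assumed 50% control risk and on early-benefit patterns chosen for illustration; the documents do not predict them, and with proportional hazards the problem disappears.

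The censoring sentence is ambiguous, not shown to be wrong. Under its less favourable reading it would cost about 5–21% of first events. The top of that range needs all drop-out to fall in the first 6 months. Lost events alone reduce precision; in the illustrations the hazard ratio moved materially only when loss was both informative and different between arms. The documents do not establish that either condition will occur. The primary CORE-OM analysis is not affected.

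**What to change.** In {20a} and the analysis plan:

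- Keep the Cox frailty model and its hazard ratio for time to first hospital-attended repetition only.
- For 6 and 12 months, report the difference in cumulative incidence between arms with a 95% confidence interval, using standard errors that allow for therapist clustering.
- Replace the censoring sentence with one stating that follow-up for this outcome ends only at 12 months, at the end of record coverage, at withdrawal of access to records, or at death (a competing event, handled as the analysis plan defines), and that questionnaire non-response does not censor.

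The cost is a few sentences and one extra table. No new data are needed, and the change can be made before the analysis.

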### Interim analyses {21b}

No formal interim analyses are planned. An internal pilot analysis will assess recruitment progression criteria 9 months from the start of recruitment; participants from this analysis will be included in the final trial analysis.

Safety data will be summarised for the DMEC during the trial; however, this will not include any primary or secondary outcome data. Follow-up rates and intervention uptake will be monitoring closely by the PSC and DMEC throughout the trial.

## Methods for additional analyses {20b}

### Subgroup analyses

For the primary outcome, exploratory analysis will compare mean scores across the three therapy modalities. When comparing individual therapies against usual care, a significance level of 1.7% will be used to adjust for multiple testing.

For the CORE-OM, a mixed model analysis will be used as in the primary outcome analysis with the addition of an interaction term between baseline SASPD and treatment and the inclusion of baseline SASPD as a covariate. For time to first repetition of self-harm leading to hospital attendance, Cox proportional hazards will be used with the addition of an interaction term between baseline SASPD and treatment and the inclusion of baseline SASPD as a covariate.

### Health economics analysis

The health economic evaluation will assess the cost-effectiveness of the self-harm-focused psychological therapy intervention relative to standard care following methods stated in the NICE methods and processes manual [41]. We will conduct both a within-trial and a decision analytic model-based cost-effectiveness analysis. The primary analysis will adopt an NHS and personal social services perspective. A sensitivity analysis will include societal costs related to patient out of pocket expenses and productivity losses. Health outcomes will be measured as quality-adjusted life years (QALYs). Intervention costs will be calculated based on the time required for therapists to deliver therapy, in addition to costs related to training and supervision.

For the within-trial analysis, healthcare costs will be obtained from hospital episode statistics data (NHS digital), combined with primary care, medication and community costs obtained from participant reported resource use questionnaires collected at 3, 6, 9, and 12 months. Health-related quality of life data will be obtained from participant responses to the CORE-6D, derived from 6 questions in the CORE-OM each with three severity responses. Health states from the CORE-6D will be mapped to UK time trade off utility values using an algorithm developed by Mavranezouli et al. [42]. QALYs will be calculated by combining health-related quality of life (HRQoL) with Office of National Statistics (ONS) mortality data. Missing data techniques consistent with the statistical modelling such as multiple imputation will be adopted to account for missing data.

The model-based analysis will use a cohort Markov model to extend results beyond the trial time horizon. Due to uncertainty in the long-term data, we will adopt a 5-year time horizon for the base case model and explore extensions (e.g. 10 years, 20 years and lifetime) in sensitivity analyses. The model will be parameterised using data collected during the trial and from published literature. All costs and benefits beyond 12 months will be discounted at 3.5% per annum.

Results will be reported in accordance with the Consolidated Health Economic Evaluation Reporting Standards (CHEERS) guidelines with cost-effectiveness summary portrayed as incremental net health benefit (INHB), incremental net monetary benefit (INMB) and incremental cost-effectiveness ratio (ICER) with maximum willingness to pay (MWtP) thresholds set over the usual NICE range £20,000–£30,000 per QALY. Uncertainty will be explored with univariate and probabilistic sensitivity analysis (PSA) with results reported on the cost-effectiveness plane (CEP) and as a cost-effectiveness acceptability curve (CEAC) over a MWtP range of £0 to £50,000 per QALY.

### Process evaluation analysis methods

A concurrent mixed methods process evaluation will be conducted to explore the implementation and acceptability of the intervention, to understand the mechanisms of change, and to explore the mediating role of context [43]. We will collect quantitative process data assessing the fidelity (as described above) and dose and acceptability of the intervention as well as trial outcome data and stakeholder characteristics. We will also conduct qualitative interviews to explore stakeholder experiences, the context, acceptability and implementation. Information about the organisation context and wider externalities will be collected from interviews, site visits and meetings with study site clinical and research teams.

We will conduct one to one interviews (telephone or face to face) with participants (*n* = 30) purposively sampled on age, gender, method of self-harm and therapy modality, to explore their experience of receiving the therapy and perceived impact on social and psychological well-being. All participants will be given the option to be invited to interview when they consent to the study. Specific participant information sheets and consent forms will be provided. Insights into mechanisms of action, intervention delivery and context will be made to help in the interpretation of trial findings and give implementation advice for any subsequent take up of intervention into MHLT provision. A purposive sample 20–30, depending upon variability, of therapists by therapy modality, study site and characteristics will be invited to be interviewed. Service managers will also be interviewed to explore how the intervention has impacted on the wider team and delivery of regular services.

Interviews will be audio recorded, using a digital audio recording device, and transcribed. During transcription, any potentially identifying information that may be contained in the interview discussions will be removed. Qualitative analysis will occur concurrently with data collection to allow for insights generated or new theories offered to be explored and tested in subsequent interviews. Analysis will focus on evidence to explore how the intervention is received, evidence to develop and refine theories of how the intervention might work and on evidence to suggest how context might affect how the intervention works in practice.

The quantitative component of the evaluation includes data from the fidelity checks described in the “Strategies to improve adherence to interventions {11c}” section. These will be combined to provide contextual data about study sites as well as providing descriptive characteristics of therapists to help understand the relationship between adherence to the intervention and the acceptability to participants that will be explored in qualitative interviews.

Several substantial amendments have been made to the trial protocol, including the introduction of incentive vouchers for completion of questionnaires at 6 and 12 months, a letter from the Lived Experience Group (LEG) to encourage follow-up completion, defining cut-off points for therapy completion, therapist assessment of trial readiness, additional fidelity checks at sessions 4, 5, and 9 and addition of new documents including a recruitment poster and a letter to potential participants confirming the unsuitability of the trial for them. Site PIs, local researchers and participants (where relevant) will be informed of all amendments following ethical and regulatory approvals. Trial registries and journals will be informed as appropriate.

